**Fig. 2 Fig2:**
[figure not shown]
Overview of enrolment and study design over time

**Fig. 3 Fig3:**
[figure not shown]
Standard Protocol Items: Recommendations for Interventional Trials (SPIRIT) Checklist

#### Study aim 1: Generate evidence on the effectiveness of Kilkari in four districts of MP

Knowledge attitudes and practices (KAP) surveys will be administered at baseline and endline containing modules on phone ownership, geographical and demographic characteristics, knowledge (danger signs during pregnancy, delivery, and postpartum; essential newborn care; nutrition; hygiene, diarrhea treatment, family planning, etc.), practices (immediate, early, and exclusive breastfeeding; complementary feeding; skin-to-skin care, etc.), RMC, and coverage for antenatal care, delivery, and postnatal care. Questions on exposure to and sources for health information content will additionally be asked to identify possible sources of contamination. The list of individuals randomized to receive Kilkari content will be provided to BBC Media Action for enrollment into Kilkari continuously throughout the implementation of the baseline survey. Following 11–12 months, participants from both study arms will be interviewed as part of the face to face endline survey.

A phone survey will be administered to all study arm participants on a rolling basis at 1 month postpartum to measure RMNCH practices, including infant feeding practices and essential newborn care as well as RMC. Methods to generate a validated phone survey tool are described elsewhere and in brief will include a face to face survey administered to women during pregnancy and with a live birth outcome in the preceding 1–4 months postpartum at the time of the household listing. A sub-sample of respondents from the initial face to face survey will be administered a second test-retest survey by a separate but similar profile of enumerator. Findings from the face to face surveys will be used to generate phone survey tools which will be implemented amongst a random sample of pregnant and postpartum women who consent to be called for the follow-up phone survey. Analyses to assess the intermodal reliability of face to face versus phone survey responses will be used to generate a validated tool. The tool developed for postpartum women will subsequently be administered to women enrolled into the iRCT during pregnancy at 1–4 months postpartum (Fig. 2).

#### Study aim 2: Identify factors which could impede the uptake of Kilkari and exposure to health information messages

User experiences with RMNCH services received in the public sector, including care received during pregnancy and childbirth, are anticipated to influence decision-making on whether recommended practices promoted through Kilkari messages are adhered to. Women’s experiences with health services during pregnancy (RMC) will be measured as part of the baseline face to face survey administered to women 5–7 months pregnant. In addition to user experiences with RMNCH, in-depth interviews (IDIs), focus group discussions (FGDs), and direct observations will be carried out among pregnant and postpartum women to identify barriers to and facilitators of pregnancy and birth registration as well as the enrolment of their mobile phone numbers in MCTS/ RCH, including the sharing of personal data and mobile phone numbers in MP and Rajasthan, India.

#### Study aim 3: Understand the factors underpinning successful receipt of calls

Following enrollment to Kilkari, we will draw from system-generated data to determine factors underpinning the successful receipt of calls not only among iRCT participants but across the 13 states where Kilkari implementation is underway. Since it is not possible to discern who listens to calls, emphasis will be placed on the mobile phone number registered to receive Kilkari content as the unit of analysis. Predicators for exposure to Kilkari content will be captured by four stakeholders: 1) government’s data system (MCTS, RCH, webservices); 2) program’s call delivery and receipt systems; 3) mobile network operator (network coverage and quality); and 4) user device characteristics (switched on, within range of network). Table 3 summarizes key indicators proposed for assessment.

**Table 3 Tab3:** Essential steps and barriers to exposure to Kilkari content in four districts of MP

	Steps in implementing Kilkari	Critical challenges	Illustrative indicators
Critical points of drop-out for Kilkari users	Pregnancy is registered on MCTS/RCH database	• Data quality, including phone numbers provided* • Delays in pregnancy identification*	Percentage of pregnant women in the MCTS/RCH with a phone number Percentage of pregnant women in the MCTS/RCH with an active phone number
	Pregnant woman becomes eligible to start receiving Kilkari messages	• Delays in registration and transfer of data across districts	Days between pregnancy identification and date of first Kilkari call
	Pregnant woman receives calls	• Variations in network coverage • Phone number may not be active • Phone number may not belong to a relevant woman or a family that contains a relevant woman—may just be a random number • Woman may not be the primary owner of the phone • Woman may not have access to phone • Phone may not be charged	Percentage of calls received out of those intended per mobile device registered to Kilkari Leading reasons for call failure
	Pregnant woman listened to the calls	• User engagement with content • User access to the phone • User mobile literacy • Phone functionality, including charge	Percentage of calls listened to out of those received on average among those enrolled to Kilkari Percentage of calls listened to on average out of all calls received Days and times during the day when messages are most likely to be listened to completely Percentage of mobile phones who listened to 75–100% of the calls on average among all phone numbers enrolled to Kilkari
	Pregnant women continues engaging with Kilkari	• Phone number may not be active • Woman may grow disinterested in continuing the service	Percentage of mobile phones with answering all weekly calls each month (4–5 depending on the month and their subscription data) Percentage of phones who received and listened to the entire Kilkari package among all phone numbers randomized to receive messages

*Less relevant to iRCT as eligible users will be identified as part of the household listing at baseline and a list of phone numbers provided to BBC Media Action for content delivery

#### Study aim 4: Determine whether users are listening to calls received

To measure user engagement with Kilkari content (behavioral performance), we will measure the proportion of calls listened to out of those received on average among the mobile phones enrolled to Kilkari. MOTECH data will be merged with IVR, call center data, and baseline face to face survey data on user characteristics, including socioeconomic status, education, phone access, mobile literacy, and numeracy, and used to identify predictors for exposure to Kilkari content. Differentials in listening patterns for each mobile device will be used to classify Kilkari users into high and low listenership groups. In addition to quantitative data analyses, qualitative interviews will be carried out to examine user perceptions of mobile messaging and use of data for program design and decision-making. Differentials in user perceptions of content by topical area as well as over time will be assessed to facilitate understanding of possible differentials in user engagement.

#### Study aim 5: Determine the value for money of Kilkari in four districts of MP

To measure the economic costs of Kilkari we will prospectively measure program, user, and health system costs in the four districts of MP. Program costs associated with the development, start-up, and implementation of program activities will be assessed using an ingredients approach for the 2018–2019 analytic time horizon. Costs to users will be assessed through face to face household surveys and include direct (out of pocket costs for drugs, supplies, consultation fees, transportation) and indirect (wages lost, child care) costs incurred by users for RMNCH careseeking. Finally, we will explore the feasibility of measuring incremental costs to the health system above and beyond those captured by the measurement of program and user costs. Collective consideration of program, user, and health system costs will allow for a societal perspective to be taken and thus a more comprehensive estimate of the full economic costs associated with the program across study arms of individuals exposed versus those not exposed to Kilkari. To measure the incremental effectiveness of Kilkari, data on changes in coverage for RMNCH careseeking and practices assessed through household surveys will be inputted into the Lives Saved Tool to generate a measure of lives saved associated with program activities. Lives saved will be used to yield an estimate of the incremental DALYs averted and ultimately a cost per DALY averted for Kilkari.

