**Methods:**

The study is an individually randomized controlled trial (iRCT) with a parallel, partially concurrent, and unblinded design. Five thousand pregnant women will be enrolled from four districts of Madhya Pradesh and randomized to an intervention or control arm. The women in the intervention arm will receive Kilkari messages while the control group will not receive any Kilkari messages as part of the study. Women in both arms will be followed from enrollment in the second and early third trimesters of pregnancy until one year after delivery. Differences in primary outcomes across study arms including early and exclusive breastfeeding and the adoption of modern contraception at 1 year postpartum will be assessed using intention to treat methodology. Surveys will be administered at baseline and endline containing modules on phone ownership, geographical and demographic characteristics, knowledge, practices, respectful maternity care, and coverage for antenatal care, delivery, and postnatal care. In-depth interviews and focus group discussions will be carried out to understand user perceptions of Kilkari, and more broadly, experiences providing phone numbers and personal health information to health care providers. Costs and consequences will be estimated from a societal perspective for the 2018–2019 analytic time horizon.

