## Background

Despite the proliferation of mobile health (mHealth) programs, evidence on their effectiveness is limited [1, 2]. mHealth solutions which provide stage-based health information messages to pregnant and postpartum women have been shown to increase knowledge, as well as the utilization of antenatal care (ANC), skilled birth attendance (SBA), and childhood immunization rates in Malawi and Zanzibar [1, 3, 4]. However, efforts to compare and/or generalize these findings are limited by the paucity of data and the quality of evaluations and evidence reporting. To date, none of the summative evaluations have reported data on exposure—defined as a function of whether users receive content (technological performance) and how they engage with that content (behavioral performance)—thus hindering efforts to understand the casual pathways between program inputs and the summative outcome measures observed [3, 5, 6].

Despite evidence limitations, maternal messaging programs are among the few examples of mHealth programs which have been successfully scaled. In four countries globally, programs exist with over one million beneficiaries: *Aponjon* in Bangladesh, *mMitra* and *Kilkari* in India, *Wazazi Nipendeni* in Tanzania, and *MomConnect* in South Africa [7]. As these programs transition from donor funding to full integration with public sector health services, renewed calls to generate evidence on their effectiveness and value for money are emerging.

In India, the Kilkari program is an outbound service that delivers weekly, stage-based audio messages about pregnancy, childbirth, and childcare directly to families on their mobile phones, starting from the second trimester of pregnancy until the child is one year old. Initiated in Bihar in 2012, Kilkari has been scaled to 13 states across India with support from Ministry of Health and Family Welfare (MOHFW) at the national level, National Health Missions (NHM) at the state level, and an alliance of donors (Bill and Melinda Gates Foundation, US Agency for International Development (USAID), Barr Foundation, and UK Department for International Development (DFID)). In the preceding 33 months, Kilkari has delivered pre-recorded audio content to an estimated 8.3 million users—making it the largest maternal messaging initiative underway globally.

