In the 13 states where Kilkari implementation is ongoing, pregnant woman or postpartum women’s data are entered into one of two health information systems registries: maternal and child health tracking system (MCTS) or reproductive and child health (RCH) system. Data, including mobile phone numbers, are collected in paper registers by frontline health workers, including auxiliary nurse midwives (ANMs) and accredited social health activists (ASHAs), and entered by data entry operators (DEOs) into the government’s electronic health records system—either MCTS or RCH system depending on the state. Data are then sent from there to the MOTECH system. Before the data are accepted by MOTECH, the system automatically runs validations to check that the mobile numbers are in the correct format, locations match location masters in the MOTECH database, and last menstrual period (LMP) and date of birth are within the Kilkari timeframe. The MOTECH system then determines the schedule for Kilkari messages based on the LMP or delivery date and the MOTECH engine provides the list of phone numbers (clients) to be called each day to the IVR system, which then calls the numbers and plays the appropriate pre-recorded message.

For the purposes of this intervention, mobile numbers will be collected directly by the research team for randomization. Pregnant and postpartum women randomized to receive Kilkari messages will receive messages from their enrollment in pregnancy through to 12 months postpartum. Women enrolled to the comparison arm (status quo) will not receive messages.

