### Measurement

Figure 2 provides an overview of enrolment and study design over time and the Standard Protocol Items: Recommendations for Interventional Trials (SPIRIT) are presented in Fig. 3 and Additional file 1. At enrollment, women will be administered a survey containing modules on phone ownership, geographical and demographic characteristics, knowledge (danger signs during pregnancy, delivery, and postpartum; essential newborn care; nutrition; hygiene, diarrhea treatment, family planning, etc.), practices (immediate, early, and exclusive breastfeeding; complementary feeding; skin-to-skin care, etc.), RMC, and coverage for antenatal care, delivery, and postnatal care. Around 6–8 weeks after the expected date of delivery, a phone survey will be administered to a random sample of the enrolled women until a target sample size of 3500 is attained (1750 each in intervention and control arms) to assess breastfeeding and newborn care practices. An endline survey will be carried out from November 2019 to February 2020 and each woman will be followed up at 12 months postpartum based on their expected date of delivery at enrollment. The endline survey will capture data on practices during pregnancy and intrapartum and postpartum periods.

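### The 2018–2019 economic horizon closes before messaging and follow-up end in February 2020, and the plan gives no stated route to the development costs it says it includes

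*Protocol article*

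**What the plan says.** The abstract of the protocol article sets one window for both sides of the ratio: "Costs and consequences will be estimated from a societal perspective for the 2018–2019 analytic time horizon". The section on measurement for study aim 5 repeats the window for the program side. It names the components as "Program costs associated with the development, start-up, and implementation of program activities" and says that these "will be assessed using an ingredients approach for the 2018–2019 analytic time horizon". The same section describes the collection: "we will prospectively measure program, user, and health system costs in the four districts of MP". User costs come from the household surveys, and no calendar limit is attached to them there. Coverage changes from those surveys feed the Lives Saved Tool, which yields the DALYs.

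The trial calendar is given elsewhere. Under Intervention description and enrollment, women in the intervention arm "will receive messages from their enrollment in pregnancy through to 12 months postpartum". Under Measurement, "An endline survey will be carried out from November 2019 to February 2020". The timing for each participant is one year after the due date recorded when she joined the trial. On the program's history, the Background says: "Initiated in Bihar in 2012, Kilkari has been scaled to 13 states across India". Under Participants and study setting, the article adds that Kilkari had not yet been implemented in the four trial districts.

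**The concern.** Two statements about the economic evaluation do not fit the rest of the article.

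- **Closing date.** The horizon ends in 2019, but messaging and 12-month outcome collection continue into 2020. The abstract therefore places some consequences outside its own window, while study aim 5 uses the survey results with no such cut.
- **Development costs.** Development is named as a component to be costed. The stated method is prospective and limited to four districts where the program was new, whereas the program itself dates from 2012 in another state.

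The cost per DALY averted is to be judged against one and three times GDP per capita (Economic evaluation). A program cost left out of the numerator lowers that ratio if effects are counted in full. The planned one-way and probabilistic sensitivity analyses vary the costs that were collected. They do not restore a component that was never collected.

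**Working it through.** The article gives a stated period and no formula for it, so there is no figure to reproduce. The check is calendar arithmetic followed by a comparison of passages.

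**Inputs from the article:** endline November 2019 to February 2020; follow-up at 12 months postpartum by expected delivery date; 72 weekly calls (24 in pregnancy, 48 postpartum); 12 to 34 weeks of gestation at randomization.

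**Assumptions:** 2018–2019 means two calendar years ending 31 December 2019; 12-month dates are spread evenly over 1 November 2019 to 29 February 2020; the 48 postpartum calls are spread evenly over 365 days; pregnancy lasts 40 weeks. The end of messaging in February 2020 is itself inferred from the 12-month rule and the endline window.

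**Start of the window.** The endline dates imply due dates from about November 2018 to February 2019. Earliest enrollment: 1 November 2018 minus 28 weeks (40 − 12) is about 19 April 2018. Latest enrollment: 28 February 2019 minus 6 weeks (40 − 34) is about 17 January 2019. Delivery to trial women therefore starts inside the horizon.

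**End of the window.**
- Endline days: 30 + 31 + 31 + 29 = 121. Days after 31 December 2019: 31 + 29 = 60. Share outside: 60/121 = 49.6%.
- Mean time outside per woman: (1 + 2 + … + 60)/121 = 1830/121 = 15.1 days, or 15.1/365 = 4.1% of postpartum time.
- Mean calls outside: 48 × 15.1/365 = 2.0.
- Scheduled calls per woman: 48 + 24 = 72 if enrolled at 12 weeks; 48 + 6 = 54 if enrolled at 34 weeks.
- Mean share of calls outside: 2.0/72 = 2.8% to 2.0/54 = 3.7%.
- Last woman: 48 × 60/365 = 7.9 calls, or 11% (of 72) to 15% (of 54).

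**Development costs, passages side by side.** Study aim 5 promises development, start-up and implementation. It measures prospectively in four districts. The program began in 2012 in Bihar and had reached 13 states. Start-up and implementation in the four districts fall within the trial period, because Kilkari was not yet running there. Development done before 2018 does not, and prospective local measurement cannot by itself observe it. The article mentions no retrospective extraction, annualisation or allocation, and no decision to treat that spending as sunk. It gives no cost figures, so neither the understatement nor a corrected ratio can be calculated.

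**The case against.** The strongest reply is that a horizon is the period to which costs are assigned, not a list of invoice dates. Earlier development spending can be annualised into 2018–2019, and the rules for that are the kind of detail an article leaves to the full protocol. The article also defers the full health-economic analysis until after the main trial. This stands to the extent that omission is possible but not stated. It does not explain how prospective collection would yield the earlier costs, and it does not remove the conflict of dates, since the article states both the horizon and the endline.

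Stronger readings that a reader might infer are not supported:

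- **Full effects set against truncated costs, so a proven bias in favour of the program.** The abstract puts consequences in the same horizon. Read literally, both sides are cut, and the ratio could move either way. Only the program-cost side can be said to be at risk of understatement.
- **User costs are lost.** Study aim 5 attaches the horizon to program costs only. User costs come from surveys with no stated cut-off, and their difference between arms could have either sign.
- **Objective 5a fails.** That objective names start-up and ongoing implementation, not development, and local start-up falls inside the trial period.
- **Most postpartum time is uncosted.** This needs 2018–2019 to be a single year ending in March 2019. Nothing in the article suggests that reading.

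It is also fair to say that including earlier development costs is a choice of method when the analysis covers four districts. But objective 5c compares Kilkari with a scenario of no messages, and against that comparator development is arguably incremental. This is a reason to show the ratio both ways.

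**Conclusion.** The point holds in a limited form. The stated horizon cannot be reconciled with messaging and follow-up to February 2020. On the calendar-year reading and even spread, about half of the endline dates fall outside it, but only about 3% to 4% of scheduled calls. The half counts any woman whose 12-month date falls even one day after the cut-off, so it does not measure lost cost. The early outcomes (breastfeeding, delivery and postnatal care) fall largely inside the window; mainly the 12-month measures cross its end.

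The development component is potentially the larger matter. It is promised, the stated method does not by itself reach it, and its treatment is undefined. The program-cost side of the cost per DALY may therefore be understated by an amount the article does not allow one to estimate. This concerns the economic aim and does not touch the primary effectiveness comparison.

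**What to change.** Set one horizon for costs and consequences, from start-up in the four districts to the last 12-month follow-up in February 2020, and use it in both the abstract and study aim 5. Take pre-2018 content and platform development costs retrospectively from the program accounts, annualise them, allocate a share to the four districts, and state the rule used. Report the cost per DALY averted with and without that component, so that the comparison with the GDP thresholds can be read both ways.

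The cost is about two more months of cost records and one extraction from program accounts. The ratio may become less favourable to the program.
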